### Hair cortisol

A hair sample is taken from the included individuals at each measurement time point for the determination of hair cortisol. Two to three thin hair strands are cut as close to the scalp as possible at the position of the posterior vertex. This protocol has been used successfully in studies for over 10 years and is well accepted by study participants [32]. The strands are first preserved and then sent to the laboratory of the Clinical Psychology of Adulthood at the University of Vienna ([name]. [name]) for hair cortisol analysis. For the determination of cortisol, commercial immunoassays with chemiluminescent detection (CLIA) from IBL, Hamburg, Germany, are used. For hair cortisol, high test–retest reliability as well as positive correlations with cortisol values from other media (e.g., saliva and urine), and with subjective stress measures are shown [33]. Hair cortisol levels of the first three centimeters from the scalp can be considered a measure of cumulative HPA axis activity over the previous three months [34].

In order to check the influence of steroids on the HPA axis, steroid doses are documented in all patients. Patients do not receive cortisone until transplantation. During transplantation, patients receive a cortisone shot of 1 g prednisolone on the day of transplantation. At the time of discharge from the hospital, the maintenance dose is 10 mg. The dose is usually reduced by 2.5 mg every 3 months and patients are no longer administered cortisone after 12 months. Furthermore, unscheduled intake of cortisone (e.g., during rejection episodes) is documented.

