### Patient baseline data, comorbidity, laboratory parameters

In addition, baseline patient data, such as age, type of underlying disease, type and duration as well as the dose (*Kt/V*) of the dialysis therapy will be obtained. Comorbidities, that may have an impact on cognitive performance (such as previous stroke, coronary heart disease, hypertension diabetes mellitus, existing dementia or depression), will be documented. Furthermore, blood parameters such as hemoglobin, creatinine, calcium, phosphorus, albumin, triglycerides, cholesterine, urea, pH-value, CO_2_, and bicarbonate will be recorded. Current medication data will be obtained from the medical records and by self-report at each testing session. In addition, changes in medication are recorded. The examinations,were executed by trained and certified medical students.

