### Statistical analysis

This is a within-group design with three measurement time points. We will investigate the proportion (percentage) of individuals that fulfill the above mentioned criteria at each given time point as estimates of prevalence of MCI and major neurocognitive impairment. Furthermore, we will conduct repeated-measures analysis of variance to investigate changes in cognitive performance over time, as well as the influence of different predictors. Cognitive performance of the individuals as a composite score and for each cognitive domain constitutes the dependent variables. The time of measurement and other control variables listed above represent the independent variables. A possible accumulation of the type I error is counteracted by an *α*-error correction (see below). The partial Eta-squared is calculated as the effect size, and the pairwise post-hoc comparisons are also corrected for multiple comparisons. The requirement of normal distribution is evaluated by the Kolmogorov–Smirnov test. Variance homogeneity is checked by Levene’s test. If the prerequisites for parametric statistics are not fulfilled, a distribution assumption-free covariance analysis according to the Quade model with rank-transformed variables is performed as an alternative.

Further questions are evaluated in terms of exploratory data analysis. Group differences are assessed using the t-test for independent samples or the Mann–Whitney-*U* test, depending on the scale level. Panels with discrete characteristics are analyzed with the *χ*^2^-test. Measures of correlation for discrete variables represent the contingency coefficients. For continuous characteristics, correlation measures according to Pearson (product-moment correlation) or Spearman (rank correlation) are used depending on the data level, in exceptional cases also according to Kendall (rank correlation without equidistance assumption).

The global significance level is set at *α* = 0.05. A false discovery rate (FDR) is calculated for *α*-error correction in multiple comparisons [35]. In the stepwise procedure, p-values are ranked in descending order; the null hypothesis is rejected if:1$$p(i) \le \frac{i}{m}\alpha$$ where *m* represents the number of *p* values and *i* the rank of the *p* value. Assuming *i* = 1, the FDR is equivalent to the Bonferroni correction.

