### Secondary outcome measures

As a secondary outcome, we will assess a distinct profile of cognitive function using standard neurocognitive tests. Furthermore, we will explore the impact and temporal development of a set of risk factors for deficits in cognitive performance. Second, we want to examine the extent to which cognitive impairment affects depression at all follow-up time points. Third, we want to assess how stressors negatively or positively affect cognitive performance. Fourth, we want to investigate to what degree cognitive performance affects the formation and development of donor-specific antibodies.

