## Discussion

The purpose of this study is to assess the extent and development of cognitive impairment in kidney transplant individuals and to provide a clear profile of cognitive function using standardized neurocognitive tests. Furthermore, we aim to evaluate whether transplantation per se leads to an improvement in cognitive performance.

There is currently no standardized test battery for kidney transplant populations, so we selected different validated tests to evaluate the different domains. Through this, it will be possible to create a neurocognitive profile of the investigated population. The tests used in kidney transplant individuals [10, 11, 41, 42] (Brief Cognitive State Examination, MoCA und 3MS, Modified Mini-Mental State Examination), which can be found in literature, are only screening tests and may underestimate the extent of cognitive impairment. We use a more comprehensive neurocognitive test battery, which is then also able to establish a neurocognitive profile in individuals after kidney transplantation. A recently published study showed a high prevalence of cognitive impairment in dialysis individuals [5], examined by the CERAD Test battery [43].

Anemia, secondary hyperparathyroidism, dialysis disequilibrium and uremic toxins (UT) have been reported as major causes of cognitive impairment accompanied by chronic kidney disease [44], as well as dialysis duration [45]. We assume that these parameters improve after transplantation and want to investigate the effect of these parameters on cognitive function.

Depression in hemodialysis individuals is characterized as one of the most common psychological aspects regarding studies on individuals with kidney failure [46]. To evaluate the frequency of depression and its effect on cognitive performance the HADS-D [26] Test will be performed. We also hypothesize that transplanted individuals suffering from depression display significantly higher cognitive impairment than transplanted individuals without depression. In one of our previous investigations, depression was significantly associated with a lower level of cognition [5]. Other studies have also found similar decline in cognition with the presence of depression [45, 47, 48]. This can be explained by the effects of symptoms of depression on domains of cognition like executive functioning and processing speed [48, 49]. A recent meta-analysis also shows that subjective stress influences the development of cognitive impairment [50].

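### For predictors measured at more than one visit, the named repeated-measures ANOVA compares patients and does not efficiently test whether cognition changes as the predictor changes (secondary questions only)

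*Protocol article*

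**What the plan says.** All places are in the protocol article.

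- **Model.** Statistical analysis: "we will conduct repeated-measures analysis of variance to investigate changes in cognitive performance over time, as well as the influence of different predictors". On what enters the model: "The time of measurement and other control variables listed above represent the independent variables". If the parametric conditions fail, "a distribution assumption-free covariance analysis according to the Quade model with rank-transformed variables is performed as an alternative".
- **Questions.** Secondary outcome measures: "we will explore the impact and temporal development of a set of risk factors for deficits in cognitive performance". The Discussion, after naming anaemia, secondary hyperparathyroidism, dialysis disequilibrium and uraemic toxins: "We assume that these parameters improve after transplantation and want to investigate the effect of these parameters on cognitive function".
- **Data.** Hair cortisol: "A hair sample is taken from the included individuals at each measurement time point for the determination of hair cortisol". Medication, in the section on patient baseline data: "Current medication data will be obtained from the medical records and by self-report at each testing session". The blood values in that same section have no stated repeat schedule. Steroid exposure is expected to change during follow-up in part A: "Patients do not receive cortisone until transplantation", followed by a taper.

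The article names no mixed model, no time-varying predictor, no change-on-change analysis, and no separation of between-patient from within-patient association.

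**The concern.** In the usual form of repeated-measures ANOVA, a continuous predictor is constant within a patient. Its main effect asks whether patients with a higher value have better average cognition. Its interaction with time asks whether that one value modifies the course. The rank-based fallback, in its standard form, also takes one covariate value per patient.

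A parameter that is expected to improve after transplantation raises a different question: does cognition move when the parameter moves in the same patient? Three visits per patient could answer it, but the named model makes little use of them for this purpose.

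Two things are at stake. A real within-patient association could be missed. And a between-patient association, which is open to confounding by stable differences such as previous stroke, diabetes or dialysis duration, could be reported as if it showed the effect of improving the parameter.

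**Working it through.** **1. The plan's own figure.** Inputs from Sample size calculation: f = 0.20, m = 3 time points, k = 2 groups, α = 0.05, power 0.80, N = 42. The correlation between visits is not given; ρ = 0.5 and sphericity are assumed.

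- λ = f²·N·m/(1 − ρ) = 0.04 × 42 × 3 / 0.5 = 10.08
- df₁ = m − 1 = 2; df₂ = (N − k)(m − 1) = 40 × 2 = 80
- Power from the noncentral F = 0.803, so N = 42 is reproduced. With ρ = 0.3 the result is 58, and with ρ = 0.7 it is 26.

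This calculation concerns the effect of time within patients. It is not a calculation for predictors, and the present point leaves it as it is.

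**2. What each test estimates.** Write cognition of patient i at visit t as

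y_it = μ_t + β_B·(person level of x) + β_W·(visit deviation of x) + u_i + e_it.

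- *Main effect of one value per patient:* regresses the patient's mean cognition on that value. Averaging over visits removes most or all of the β_W signal, so the test responds mainly to β_B.
- *Baseline value by time:* regresses the visit contrasts of cognition on the baseline value. It picks up part of β_W, because the baseline deviation affects baseline cognition, but it ignores the later values of x.
- *Change-score correlation:* relates the baseline-to-12-month change in x to that in y. It targets β_W but leaves out the 3-month visit.
- *Within-patient model:* uses all visit deviations, with visit effects removed.

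**3. Simulation.** All of these inputs are assumptions; the article gives none. There are three visits, a predictor with between-person SD 1 and visit-level SD 1, and between-person and residual variance of cognition of 0.5 each. Power or rejection rate at two-sided 0.05, n = 50:

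| Test | Within-patient slope 0.35 only | Between-patient slope 0.4 only |
|---|---|---|
| Main effect (baseline value or person mean) | about 5–14% | about 60–95% |
| Baseline value by time | about 35% | about 5% |
| Change-score correlation | about 91% | about 5% |
| Within-patient model | over 99% | about 5% |

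The ranges for the main effect have two sources: which single value is entered, and how the effect is built. If the within-patient effect acts on deviations from the observed person mean, averaging cancels it and the main effect stays near 5%. If it acts on the visit-level component itself, some signal survives in the averages.

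With n = 25 (an illustrative half of the follow-up target of 50) and the within-patient slope of 0.35, the main effect has about 4–9%, baseline by time 18%, the change-score correlation 61–64% and the within-patient model 90–92%.

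**4. Sensitivity.** With other assumptions (within-patient slope 0.4, all SDs 0.7, n = 50) the results are 8% for the baseline main effect, 11% for the person-mean main effect, 25% for baseline by time and 97% for the within-patient model. With equal within- and between-patient slopes of 0.35, the main effect has 75–92% at n = 50, but it cannot tell the two apart.

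**The case against.** **The article does not say that one fixed value is entered.** That is true; it is a property of the standard form of the named method. A univariate form with patient as block and visit as factor would accept a visit-specific value and yield a within-patient slope. So the plan can be rescued by wording, but nothing in it points to that form.

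**Many aims are between-patient or baseline questions.** This stands. The Discussion compares transplanted patients with and without depression, and is interested in hair cortisol as exposure before transplantation. The stress variables are introduced as possible mediators and moderators, and moderation is what the interaction with time tests. For these aims the named model is suitable. The impact and the temporal development of risk factors can also be read as two separate questions. The sentence on improving parameters is the clearest exception.

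**Blood values may be measured only at baseline.** This also stands. Repetition is explicit for hair cortisol and medication. For haemoglobin and the other laboratory values the point applies only if they are repeated.

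**Exploratory correlations are available.** Correlations of change scores would do quite well (about 91% at n = 50), but the article does not say that correlations will be run on changes.

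**Stronger readings that a reader might infer.** One is that the planned test produces false positives. It does not: in the between-patient scenario a real slope of 0.4 was built in, and the main effect detects it correctly. The error would arise only if that result were read as an effect of change, and the article does not commit itself to that reading. Another is that the plan would miss within-patient effects altogether. The interaction with time and the possible change-score correlation show that this goes too far.

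**Conclusion.** The point holds in a limited form. For predictors measured at more than one visit, the named model is not an efficient test of whether a patient's cognition changes with that patient's predictor. In the setting examined, its two terms have about 5–14% and 35% power, against over 99% for a within-patient model. These figures rest on assumed variances and a purely within-patient effect. The gap shrinks when within- and between-patient slopes are similar, but the named model's main effect then still cannot separate them.

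The scope is the secondary, exploratory questions about changing predictors: certainly hair cortisol and medication, and laboratory values if they are repeated. Between-patient and baseline aims, the primary comparison over time and N = 42 are unaffected. The change is worth making because it is cheap and uses data already being collected.

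**What to change.** For each predictor measured at more than one visit, replace the ANOVA covariate with a linear mixed model: random patient intercept, visit as a factor, and the predictor entered as two terms, the person mean and the visit-specific deviation from it. Base any statement about change in the predictor on the deviation term only, and report the person-mean term as a between-patient association. Keep the ANOVA form for fixed or baseline predictors such as age, donor type or pre-transplant cortisol. State which laboratory values are repeated and at which visits.

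The cost is a change in the analysis text and two coefficients per predictor to report, with no new patients or procedures. Two limits should be stated alongside. The visit factor absorbs improvement that all patients share, so the deviation term rests on patients whose predictor changes more or less than the average. And time-varying confounding, for example by steroid exposure or rejection episodes, remains, so the deviation term shows an association and not proof of cause.

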### Sample size calculation

In order to investigate the prevalence of MCI or dementia, all individuals currently registered on the local transplant list, who are able to consent and agree to participate in the study, will be included. Currently, this list includes 142 individuals (75 individuals are in status T (transplantable), 67 individuals are in status NT (non-transplantable).

With regard to outcome measures, previous studies have shown highly significant improvements in some domains after transplantation [36], but have not reported effect sizes or statistical parameters that could be used to calculate effect sizes. Harciarek and colleagues [37, 38] report moderate to strong “time × comparison with healthy controls” interaction effects. We therefore conservatively expect to find low to medium effect sizes. For the detection of low to medium (*f* = 0.20) within-person effects with 3 measurement time points and 2 groups using a repeated-measures ANOVA as explained above, a power (1 – *β* (type II error probability) of 0.80 and a type-I error probability (*α*) of 0.05, a sample size of 42 is necessary [39, 40]. We therefore aim for a sample size of 50 persons for the follow-up measurements.

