### Primary outcome measure

The primary outcome measure will be cognitive performance. (a) We will compare cognitive performance before and after kidney transplantation, up to 12 months after transplantation in a population of patients who did not yet receive kidney grafts before enrollment in the study (part A) and (b) we will also investigate the development of cognitive performance over a period of 12 months in a population of patients who already received kidney grafts before enrollment in the study (part B).

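### The power of 0.80 with 42 patients is for one uncorrected test, but the analysis covers a composite and four domains under an FDR correction, and none is named as primary

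*Protocol article*

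**What the plan says.** All references are to the protocol article.

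- **Primary outcome measure:** "The primary outcome measure will be cognitive performance". It is examined before and after transplantation in Part A, and over 12 months in already transplanted patients in Part B. No score is singled out.
- **Statistical analysis:** "Cognitive performance of the individuals as a composite score and for each cognitive domain constitutes the dependent variables". The cognitive test battery section and Table 2 list four domains (visual memory, verbal memory, attention, executive function), so there are five dependent variables.
- **Statistical analysis, same paragraph:** "A possible accumulation of the type I error is counteracted by an" alpha correction. The method is the FDR step-up rule, in which the i-th ranked p-value is compared with (i/m) × alpha. The section itself notes that the step i = 1 equals Bonferroni. Exploratory questions come only afterwards, so the correction is not confined to them.
- **Sample size calculation:** the study is sized for f = 0.20 for "within-person effects with 3 measurement time points and 2 groups using a repeated-measures ANOVA as explained above", with power 0.80 and alpha 0.05, and concludes that "a sample size of 42 is necessary". The target for follow-up is 50. The correction is not mentioned.
- **Secondary outcome measures:** a profile of cognitive function is listed as secondary.

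**The concern.** The sample size section points back to the ANOVA described just before it, but leaves out the correction attached to that ANOVA. If the five scores share one FDR family, a score may have to reach p ≤ 0.01 instead of p ≤ 0.05, and the stated 0.80 no longer describes the planned test.

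Two things are at stake. The chance of detecting the assumed effect may be lower than readers are told. And because no score is named, it is open which result would count as a positive primary finding. The second matters most if change is confined to a few domains. The sample size section makes that a realistic case, since it cites earlier work that found improvement in only some of them.

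**Working it through.** **Inputs from the article:** f = 0.20, m_t = 3 time points, k = 2 groups, alpha = 0.05, power 0.80, N = 42, target 50, five dependent variables.

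**Assumptions not in the article:** correlation between time points r = 0.5, and sphericity.

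**Formula (noncentral F):** lambda = f² × N × m_t / (1 − r), df1 = m_t − 1 = 2, df2 = (N − k)(m_t − 1).

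**Step 1. Reproduce 42.** lambda = 0.04 × 42 × 3 / 0.5 = 10.08; df2 = 40 × 2 = 80; critical F at 0.05 = 3.11; power = 0.803. With N = 41 it is 0.793 and with N = 40 it is 0.782. So 42 is exactly the figure for one test at uncorrected 0.05. For N = 50, lambda = 12, df2 = 96 and power = 0.873.

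**Step 2. First FDR step with five variables.** The threshold is 0.05 / 5 = 0.01. For N = 42 the critical F is 4.88 and power is 0.586; for N = 50 they are 4.83 and 0.693. Power of 0.80 at this level needs 61 patients, or 62 with equal groups.

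**Step 3. The FDR procedure itself.** Step 2 is the strictest threshold. The step-up rule relaxes it as more variables show an effect. Simulation (8,000 runs per scenario, five variables, correlation between variables 0 or 0.5) gives this power for one given affected variable:

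| Variables truly affected | N = 42 | N = 50 |
|---|---|---|
| 1 of 5 | 0.59–0.60 | 0.70 |
| 2 of 5 | 0.65–0.67 | 0.75–0.76 |
| 3 of 5 | 0.69–0.72 | 0.80 |
| 5 of 5 | 0.76–0.77 | 0.85–0.86 |

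With 42 patients every scenario is below 0.80. With 50, 0.80 is reached from about three affected variables upwards. The simulation treats the five scores as equally correlated and does not build the composite from the domains.

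**Step 4. Dependence on the unstated correlation.** Power at alpha 0.01 (the first FDR step):

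| r | N = 42 | N = 50 |
|---|---|---|
| 0.3 | 0.40 | 0.50 |
| 0.5 | 0.59 | 0.69 |
| 0.6 | 0.72 | 0.81 |
| 0.7 | 0.86 | 0.93 |

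**Step 5. Separate tests in Parts A and B.** The calculation assumes two groups, whereas the primary questions concern time within each part. If 50 is the total, each part has about 25: lambda = 0.04 × 25 × 3 / 0.5 = 6, df2 = 24 × 2 = 48, and power at alpha 0.05 is 0.56. If 50 is per part, it is 0.87. If the two parts also shared alpha at 0.025 each, 50 per part would give 0.80.

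**The case against.** **Five equal-ranking primaries.** A reader might infer that the plan has five co-primary outcomes. It does not say so. It names one construct, lists the composite first, and places the cognitive profile among the secondary outcomes. The Introduction explains the profile as whether one domain is more affected than others. Composite as primary and domains as secondary is thus a natural reading. This part of the objection stands. It does not settle the matter, because the article nowhere names the composite, and it puts composite and domains side by side under one correction.

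**Power is really 0.59 or 0.69.** A reader might also take these as the true power. They are the floor, reached when only one of five variables changes. The composite summarises the same battery, so a real change in it normally brings some movement in the domains, and power under the step-up rule is then higher.

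**The target is 50, and the correlation may be higher.** Both are fair. Fifty gives some margin, but the article does not say whether the extra eight are meant for dropout, and they do not restore 0.80 when one or two variables change. A correlation of 0.6 or more would restore it with 50 patients even at the strictest threshold, but a lower one makes matters worse, and the article states none.

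**The hierarchy belongs in the full protocol or analysis plan.** A condensed article may leave such detail out. Here, however, the dependent variables, the correction and the power calculation are all stated, and it is these stated parts that do not fit together.

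**Conclusion.** The point holds in a limited form. The 0.80 is an uncorrected single-test figure, attached to an analysis of five scores under an FDR correction, with no score named as primary. If all five share the correction, per-variable power is about 0.59 to 0.77 with 42 patients and 0.70 to 0.85 with 50, so 0.80 is not assured. This rests on r = 0.5 and sphericity, inferred only because they reproduce 42, and on a family of five.

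The documents do not show that the study is underpowered. If the composite is the single primary variable, the correction problem disappears. Nor can one say that the calculation would then match separate tests in the two parts. It assumes two groups, and it is not stated whether 42 and 50 are per part or in total. The cohort of 100 in the Abstract could mean 50 per part, but nothing says so.

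**What to change.** 1. In Statistical analysis and Primary outcome measure, name the composite z-score as the single primary dependent variable, tested at 0.05. Make the four domain scores secondary, in line with the secondary cognitive profile, with the FDR correction over those four.
2. If all five are to stay primary, restate the power in the Sample size calculation as the range under the FDR procedure (about 0.59 to 0.77 with 42, about 0.70 to 0.85 with 50), together with the assumed correlation.
3. In the same edit, state whether 42 and 50 are per part or in total, and whether the 0.80 refers to a pooled two-group effect or to time within each part. If they are totals and the tests are separate, restate the power (about 0.56 with 25 per part).
4. State whether the part-wise primary tests answer separate questions, each at 0.05, or share the alpha.

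The cost is a few sentences. Naming the primary variable needs no extra patients; its downside is that domain results become secondary. If item 3 shows that 50 is the total for two separate tests, the lower power must be either accepted openly or met with more patients.

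### The effect size named for the ANOVA of change, partial eta-squared, is biased upward in small samples and has no sign, although the trial asks whether cognition improves

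*Protocol article*

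**What the plan says.** The Statistical analysis section of the protocol article describes the design so: "This is a within-group design with three measurement time points". For the main analysis, "we will conduct repeated-measures analysis of variance to investigate changes in cognitive performance over time", with the composite score and each cognitive domain as dependent variables. It then fixes the effect measure: "The partial Eta-squared is calculated as the effect size". The same sentence adds that "the pairwise post-hoc comparisons are also corrected for multiple comparisons", without naming an estimate or an interval for those comparisons.

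The Discussion gives a directional aim: "we aim to evaluate whether transplantation per se leads to an improvement in cognitive performance". The Primary outcome measure section asks the question separately in part A (before against after transplantation) and part B (course over 12 months in patients already transplanted).

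The Sample size calculation section expects modest effects: "We therefore conservatively expect to find low to medium effect sizes". It uses f = 0.20, three time points, two groups, power 0.80 and α = 0.05, arrives at 42, and aims for 50 persons at follow-up. It does not say how the 50 divide between the parts. The abstract gives a cohort of 100.

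**The concern.** Partial eta-squared is the time sum of squares divided by the time plus error sums of squares. Two properties follow.

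- It cannot fall below zero, so sampling noise always pushes it upward. A part or domain in which nothing changes still gets a positive value, and a real effect is overstated on average. The overstatement grows as the group gets smaller.
- It has no sign. A rise and a fall of equal size give the same value.

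The trial asks whether cognition improves and by how much, and the article says that better knowledge of course and profile matters for designing future studies. It also notes that an earlier study gave no effect sizes usable for planning. A later team that took these values at face value would plan on effects that are too large and would not see their direction.

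**Working it through.** **Inputs.** From the protocol article: three time points, f = 0.20, two groups, power 0.80, α = 0.05, stated sample size 42, target 50. Assumed, because the article does not give them: visit correlation ρ = 0.5, sphericity, and the number of patients per part.

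**1. Reproduce the stated sample size.** Noncentral F with λ = f²·N·m/(1 − ρ), m = 3, df1 = 2, df2 = 2(N − 2).

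- N = 42, ρ = 0.5: λ = 0.04 × 42 × 3 / 0.5 = 10.08, df2 = 80, power 0.803. The figure of 42 is reproduced.
- N = 50, ρ = 0.5: λ = 12, df2 = 96, power 0.873.
- Other correlations do not reproduce it: ρ = 0 needs 82, ρ = 0.3 needs 58, ρ = 0.7 needs 26.

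So ρ = 0.5 is the working assumption below.

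**2. Mean of partial eta-squared with no true change.** Under sphericity it follows Beta(df1/2, df2/2), with mean df1/(df1 + df2). For one part with n patients, df1 = 2 and df2 = 2(n − 1), so the mean is 1/n. The size of the visit correlation does not enter.

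| Setting | df2 | Mean with no change |
|---|---|---|
| One part, n = 20 (assumed) | 38 | 2/40 = 0.050 |
| One part, n = 25 (assumed equal split of 50) | 48 | 2/50 = 0.040 |
| One part, n = 50 | 98 | 2/100 = 0.020 |
| Joint two-group model, 50 in total | 96 | 2/98 = 0.0204 |

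Simulation (50,000 data sets per setting) gave 0.040 at n = 25, both with equal correlations and with a non-spherical pattern, and 0.020 at n = 50.

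**3. Mean when the planned effect is true.** With unit variance, f = 0.20 gives a time component of 3 × 0.04 = 0.12 per patient and an error component of 2 × (1 − 0.5) = 1.00. The population partial eta-squared is 0.12/1.12 = 0.107. Simulated in one group:

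| n | Mean partial eta-squared | Ratio to 0.107 | Mean partial epsilon-squared |
|---|---|---|---|
| 50 | 0.123 | 1.15 | 0.105 |
| 25 | 0.139 | 1.30 | 0.103 |

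Partial epsilon-squared, (SS time − df1 × MS error)/(SS time + SS error), averaged 0.000 with no change.

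The population value depends on ρ: 0.12/1.52 = 0.079 at ρ = 0.3 and 0.12/0.72 = 0.167 at ρ = 0.7. The proportional overstatement is larger at the lower correlation and smaller at the higher one.

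**4. Direction.** Reversing the sign of the same change at n = 25 gave 0.140 instead of 0.139, a difference within simulation error.

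**The case against.** Partial eta-squared is the customary companion of a repeated-measures ANOVA and belongs to the same family as the f used for planning. The article does not contradict itself here. It is also a condensed text, and confidence intervals or change estimates may stand in a fuller document. That holds: the absence of an interval is not the point. The point is the measure that the article does fix.

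Four stronger readings are tempting, and the article does not support them.

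- *A null part will show 0.04.* No section gives 25 patients per part. With 50 in a part, or in the joint two-group model behind the sample size, the figure is about 0.02.
- *The report could not tell decline from improvement.* The pairwise post-hoc comparisons are made on z-scores and can show direction, as can the proportion impaired at each time point. Only the index lacks a sign, and epsilon- and omega-squared do not supply one.
- *Noise alone can exceed the planned effect, so the index misleads about significance.* At n = 25 the null 95th percentile is 0.117, above 0.107. But that percentile is just the F-test cutoff at α = 0.05 on another scale. It reflects limited power at an assumed n and is no separate defect.
- *Partial eta-squared is the only effect measure in the plan.* The exploratory analyses also name correlation and contingency coefficients. It is the only effect size named for the ANOVA of change.

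Nor does any section plan to rank domains by this index or to compare it between parts of different size, so harm from such uses is conjecture. What remains is an upward-biased, unsigned index for a question about improvement, when a signed estimate on an interpretable scale is available from the same data.

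**Conclusion.** The point holds with modest weight. For the analysis of change, the named effect size averages about 0.02 with 50 patients and no change, and 0.04 to 0.05 if a part has 25 or 20 patients. If the planned effect is true, it is overstated by roughly 15% at n = 50 and 30% at n = 25. The null figures rest on the number per part, which the article does not state. The 15% and 30% also rest on a visit correlation of 0.5 and sphericity; that correlation was chosen because it reproduces 42.

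A reader might infer that the tests or the sample size are wrong. They are not affected: the bias concerns the reported magnitude only. The F test, its type I error, the post-hoc tests and the figure of 42 stand.

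**What to change.** Replace the effect-size statement in the Statistical analysis section with wording such as:

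> The main effect measure is the mean within-person change in z-score from baseline to month 3 and from baseline to month 12, with 95% confidence interval, separately for part A and part B, for the composite score and each cognitive domain. If a variance-explained index is also given, it is the bias-corrected partial epsilon-squared or omega-squared.

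The cost is a change of wording. The z-scores are already planned, so no further data, visits or patients are needed. The one drawback is that reported variance-explained values become somewhat smaller, for example about 0.103 instead of 0.139 on average at n = 25 under the assumptions above.
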